**Methods:**

The short-term and mid-term changes produced by different therapies on subjects with non-specific chronic neck pain will be studied. The sample will be randomly divided into three groups: manual therapy, therapeutic exercise, and placebo. As dependent variables of the study, we will take (1) Overall Balance Index, measured through a dynamic stabilometric platform; (2) pain, based on the visual analog scale and the Pressure Pain Threshold; (3) cervical disability, through the neck disability index. The findings will be analyzed statistically considering a 5% significance level (*p* ≤ 0.05).

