### Secondary objective

A secondary objective is to analyze the evolution of cervical pain and disability according to the treatment applied and the relationship with changes produced on PS.

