### Hypothesis

Experimental treatments have a greater beneficial effect on PS and pain of subjects with NCNP than sham treatment. The improvement in PS is linked to an improvement in the subject’s pain.

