#### Overall Balance Index (OBI)

We obtain the OBI measurement through a dynamic stabilometric platform (Balance System™ SD; Biodex, Shirley, NY, USA). The General Stability Test is applied at level of difficulty 4, with 1 being the most and 8 the least difficult level. The platform is free in the anterior-posterior and medial-lateral axes, and it allows one to obtain the OBI through deviations with respect to a zero point established before the test, with the platform stable. Two 20-s tests are performed, with 1 min between each test, with the score of the second test chosen for the statistical analysis. The index is calculated through the anterior-posterior and medial-lateral relationship + standard deviation [40, 41].

These variables will be measured in the pre-evaluation, first evaluation (week 2), second evaluation (week 4, short-term), and third evaluation (week 12, medium term). These evaluations will be carried out by an evaluator trained in these procedures, and the data will be stored in an Excel document.

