### Statistical analysis

The statistical analysis will be carried out using IBM-SPSS Statistics 24 software. The normality test applied to all the variables will be the Kolmogorov-Smirnov test. For the contrast of intragroup hypotheses, Student’s *t* test for paired variables will be applied in the case of parametric distributions and Kruskal-Wallis *H* for non-parametric distributions. For the intergroup hypothesis contrast, one-factor analysis of variance (ANOVA) will be used in the case of parametric distributions and Kruskal-Wallis *H* for non-parametric distributions. Post hoc analysis will be obtained through Bonferroni’s contrast for parametric distributions and Mann-Whitney’s *U* for non-parametric ones. Associations between pain (clinical improvement) and PS will be analyzed through Pearson’s *R* or Spearman’s rho. The confidence level used will be 95% (0.05), and the power of the study will be 90% (0.1).

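### Within-arm paired tests have hypothesis status, while the objective on evolution by treatment has no specified between-arm test of change and baseline values go unused

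*Protocol article*

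**What the plan says.** The Hypothesis section is comparative in its first sentence: "Experimental treatments have a greater beneficial effect on PS and pain of subjects with NCNP than sham treatment". Its second sentence is an association between improvement in postural stability and improvement in pain. The Secondary objective is to "analyze the evolution of cervical pain and disability according to the treatment applied", together with the relation to changes in postural stability.

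Four outcomes are named in the abstract's Methods: the balance index ("As dependent variables of the study, we will take (1) Overall Balance Index"), "pain, based on the visual analog scale and the Pressure Pain Threshold", and "cervical disability, through the neck disability index". The schedule stands under Overall Balance Index: "These variables will be measured in the pre-evaluation, first evaluation (week 2), second evaluation (week 4, short-term), and third evaluation", the last of these at week 12. There is thus one baseline and three follow-up values per outcome.

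The Statistical analysis section then sets two kinds of test. The first begins "For the contrast of intragroup hypotheses" and assigns Student's paired t test, with Kruskal-Wallis as the non-parametric alternative. The second is for differences between groups: a one-factor ANOVA or Kruskal-Wallis test, followed by Bonferroni or Mann-Whitney post hoc comparisons. No baseline covariate, visit factor or arm-by-visit term is named. The section does not say whether the ANOVA is run on raw follow-up values or on change.

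**The concern.** How an outcome evolves according to treatment is a question about differences between arms in change over time. The only test that the plan expressly ties to change over time is run inside each arm separately. A significant change in one arm and a non-significant change in another does not show that the arms differ. Each paired test compares its arm with zero, so it also picks up natural improvement, regression to the mean and the effect of taking part. Patients enrolled with current pain may well improve somewhat in every arm, sham included.

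The stakes go beyond tidiness. The Discussion intends to infer from the behaviour of the two therapies whether postural instability has a more structural or a more central origin. Different within-arm verdicts would invite that inference without supporting it. Separately, a one-factor comparison that ignores baseline gives up precision that the collected data could supply, in a trial of 66 patients.

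**Working it through.** The plan gives no figure of its own on this point, so there is nothing to reproduce first.

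**Inputs from the protocol article**
- Arms: 3 (abstract, Methods: "The sample will be randomly divided into three groups: manual therapy, therapeutic exercise, and placebo").
- Outcomes: 4 (balance index, VAS, pressure pain threshold, Neck Disability Index).
- Follow-up visits: 3 (weeks 2, 4 and 12).
- Patients: 66, with 15% losses allowed for (Sample size calculation). 66 / 3 = 22 per arm; 22 × 0.85 = 18.7, taken as 19 evaluable.
- Design difference 0.098, SD 0.10 (Sample size calculation).

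**Assumptions**
- Within-arm tests are two-sided at 5%.
- The SD of the change score is not given, so the true change is expressed as d, in units of that SD.
- All three arms have the same d, so the true treatment difference is zero. Arms are independent.

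**1. Number of within-arm tests.** If each follow-up is compared with baseline only: 3 arms × 4 outcomes × 3 visits = 36. The document states neither this count nor which pairs of visits are compared. All six pairs of the four time points would give 3 × 4 × 6 = 72. All are paired t tests only if every variable passes the normality check.

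**2. Chance of mixed verdicts.** Let p be the power of one paired t test with n = 19, from the noncentral t with 18 degrees of freedom and noncentrality d√19. The three arms do not all get the same verdict with probability 1 − p³ − (1 − p)³.

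| Shared true change d (SD of change) | p | Mixed verdicts |
|---|---|---|
| 0 | 0.05 | 14% |
| 0.1 | 0.070 | 20% |
| 0.2 | 0.131 | 34% |
| 0.3 | 0.236 | 54% |
| 0.4 | 0.379 | 71% |
| 0.45 | 0.459 | 75% |
| 0.5 | 0.541 | 75% |
| 0.6 | 0.696 | 63% |
| 0.8 | 0.909 | 25% |
| 0.9 | 0.960 | 12% |
| 0.98 | 0.981 | 6% |

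Worked example at d = 0.3: 1 − 0.236³ − 0.764³ = 1 − 0.013 − 0.446 = 0.54.

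**3. The same on the balance-index scale.** With a pre-post correlation ρ, the SD of change is 0.10 × √(2(1 − ρ)), which equals 0.10 at ρ = 0.5. With 20 per arm and ρ = 0.3 / 0.5 / 0.7, mixed verdicts occur in 73% / 74% / 54% of trials when every arm changes by half the design difference (0.049). They occur in 17% / 4% / 0.1% when every arm changes by the full 0.098. In simulation at ρ = 0.5 (40,000 runs per setting), one ANOVA on change across the three arms rejects in about 5% at every shared change tried.

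**4. What baseline adjustment adds.** With equal variances σ² at baseline and follow-up, the residual variance for a between-arm comparison is σ² on raw follow-up values, 2(1 − ρ)σ² on change, and (1 − ρ²)σ² with baseline as covariate. For ρ = 0.3, 0.5 and 0.7 these factors are:
- raw follow-up: 1, 1, 1;
- change: 1.4, 1.0, 0.6;
- baseline-adjusted: 0.91, 0.75, 0.51.

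Apart from the one degree of freedom spent on the covariate, adjustment is no worse than either alternative at each value. The size of the gain depends on a correlation that the document does not give.

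**The case against.** The strongest reply is that the plan does contain a between-arm test with post hoc comparisons, and that this is the natural place for the comparative hypothesis. This stands. Randomisation makes baseline means equal in expectation, so a one-factor ANOVA at a follow-up visit estimates the same treatment effect as a comparison of changes, even on raw values. It is valid, though it may be less precise. An ANOVA on change scores would also fit the wording. A journal article may leave the choice of dependent variable to a fuller document.

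A reader might infer that treatments will be judged by setting within-arm p-values side by side, or that the paired tests are the only planned analysis bearing on treatment. The document supports neither reading. It nowhere says that within-arm results decide a treatment claim. Nor is every hypothesis comparative, since one concerns an association.

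A reader might also multiply 36 tests into a family-wise error: 1 − 0.95³⁶ = 84%. That needs independent tests and no change in any arm. Outcomes measured in the same patients against one shared baseline are not independent, and 84% is not an error rate for any treatment claim.

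Finally, the range 0.3 to 0.6 SD has no source in the document and brackets the maximum of the curve, where power is near one half. Outside it, disagreement is much rarer.

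What the reply does not remove is that the section prescribes within-arm hypothesis tests, and specifies a one-factor between-arm test with no term for baseline or visit, for an objective about evolution by treatment.

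**Conclusion.** The point holds as a question of specification and precision. Within-arm tests are given a role that they cannot serve, the evolution objective lacks a specified between-arm test of change, and baseline values already collected are left out of the between-arm comparison. The planned ANOVA is not invalid.

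The risk of misleading within-arm verdicts depends on the size of the shared change. It is large for small-to-moderate change (54% to 75% at 0.3 to 0.6 SD), modest with none (about 14%), and small near 1 SD (about 6% with 19 per arm, about 4% with 20). These figures rest on two-sided 5% tests, independent arms and identical true change. They would do harm only if someone read the paired tests across arms, which the plan does not announce but does not rule out.

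**What to change.** In the Statistical analysis section:

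1. Take the within-arm comparisons out of the hypothesis tests. Report within-arm mean changes with 95% confidence intervals as description.
2. Replace the one-factor ANOVA with one model per outcome over weeks 2, 4 and 12, with arm, visit, arm × visit and the baseline value as terms and the patient as the repeated unit. Report between-arm differences at each visit with 95% confidence intervals. At minimum, use a baseline-adjusted comparison of arms at each visit.
3. State that conclusions about treatment rest only on the between-arm differences.

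The order of priority among the visits is for the sponsor to set.

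The cost is wording. The data are already scheduled, the named SPSS package fits such models, and no patients or visits are added. The one loss is fewer p-values to report.

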### Sample size calculation

The sample size was calculated using the Granmo calculator v.7.12. Based on the analysis of the variance of means, and estimating an alpha risk of 5% (0.05), a beta risk of 10% (0.10), a unilateral contrast, a typical deviation of 10% (0.10), a minimum difference to detect of 9.8% (0.098) which is based as the minimum clinically important differences in OBI [42], and a rate of follow-up losses of 15%, 10 subjects are required in each group, assuming that there are three groups. Finally, we will include 66 patients who will be divided into three groups, each group with at least 20 subjects, so as to overcome this value to assume the possible loss of follow-up.

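### Kruskal-Wallis H, a test for independent groups, is named for within-group comparisons of the same participants over time

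*Protocol article*

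**What the plan says.** The Statistical analysis section of the protocol article first sets a gate: "The normality test applied to all the variables will be the Kolmogorov-Smirnov test". The result decides between a parametric and a rank-based test.

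The within-group rule opens "For the contrast of intragroup hypotheses" and continues: "Student’s *t* test for paired variables will be applied in the case of parametric distributions and Kruskal-Wallis *H* for non-parametric distributions".

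The between-group rule follows directly: "For the intergroup hypothesis contrast, one-factor analysis of variance (ANOVA) will be used" when the distribution is judged parametric, with Kruskal-Wallis H again as the alternative.

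The measurement schedule is given under Outcome measures, at the end of the Overall Balance Index (OBI) subsection. All outcomes are taken at the "pre-evaluation, first evaluation (week 2), second evaluation (week 4, short-term), and third evaluation (week 12, medium term"). Each participant therefore contributes up to four values per outcome. No rank test for paired or repeated data is named anywhere in the article.

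**The concern.** A within-group comparison sets a participant's follow-up value against the same participant's baseline. The paired t test respects that. Kruskal-Wallis H takes its null distribution from independent samples, so it would treat 22 pairs as 44 unrelated observations.

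The normality gate applies to every variable, so OBI, VAS, PPT or NDI could each be sent down this branch. The secondary objective concerns how pain and disability evolve under each treatment, and the abstract promises short-term and mid-term changes. The within-group tests serve those aims directly. One results table could then show a paired analysis for one outcome and an unpaired analysis for the next, and a difference in significance between them could come from the test and not from the participants.

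**Working it through.** The article gives no figure for this rule, so there is none to reproduce. The check has three steps.

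**Inputs.** From the article: 66 participants in three groups (Sample size calculation), so 66/3 = 22 per group if equal; significance level 0.05; four visits. Assumed, because the article gives neither: the visit-to-visit correlation r, shown from 0 to 0.9, and a true change of 0.5 SD. All tests are two-sided.

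**Step 1: why the null distribution is wrong.** With two visits of n participants each and N = 2n pooled values, Kruskal-Wallis H is the squared difference in mean ranks divided by the variance expected under independence:

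N(N+1)/12 × (1/n + 1/n) = 44 × 45/12 × 2/22 = 15.

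If the two visits have rank correlation ρ, the true null variance is approximately 15 × (1 − ρ). H then behaves like (1 − ρ) times a chi-square variable on 1 degree of freedom, and the true false-positive rate is about P(χ² > 3.84/(1 − ρ)). For bivariate normal data, ρ = (6/π) × arcsin(r/2).

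- r = 0.3: ρ = 0.288; 3.84/0.712 = 5.39; rate 2.0%
- r = 0.5: ρ = 0.483; 3.84/0.517 = 7.42; rate 0.6%
- r = 0.7: ρ = 0.683; 3.84/0.317 = 12.1; rate 0.05%

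**Step 2: simulation, two visits.** Bivariate normal data, n = 22, 8,000 runs per setting.

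| r | Null rejection, Kruskal-Wallis | Null rejection, Wilcoxon signed-rank | Power at 0.5 SD, Kruskal-Wallis | Power at 0.5 SD, Wilcoxon signed-rank |
|---|---|---|---|---|
| 0 | 5.0% | 4.5% | 35% | 32% |
| 0.3 | 2.2% | 4.5% | 33% | 45% |
| 0.5 | 0.8% | 4.3% | 30% | 57% |
| 0.7 | 0.1% | 4.3% | 28% | 79% |
| 0.9 | 0.0% | 5.1% | 24% | 99.8% |

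The null column agrees with step 1, allowing for the large-sample approximation. With 20 per group, the article's stated minimum, the figures at r = 0.5 are 1.1% against 5.2% for null rejection and 27% against 54% for power.

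**Step 3: simulation, all four visits together.** n = 22, 4,000 runs per setting, with the 0.5 SD change present at all three follow-ups. At r = 0.5, Kruskal-Wallis rejects a true null 0.4% of the time and Friedman 4.4%; power is 19% against 51%. At r = 0.7 the null rates are 0.03% and 4.5%, and power is 14% against 75%.

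**The case against.** Several points can be made for the plan, and most of them stand as limits on the consequence.

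- **The main comparison is unaffected.** The primary objective and the main hypothesis are between-group questions, and for three independent arms Kruskal-Wallis is suitable. Within-group tests cannot show superiority over sham. This stands.
- **Only one conditional branch is affected.** The rule applies only when a variable fails the Kolmogorov-Smirnov test, which often misses skewness at this sample size. For an assumed lognormal variable (log-SD 0.5, n = 22), it fails about 35% of the time with the Lilliefors version and about 2% with the plain version. Few variables, or none, may reach this branch. This stands too.
- **The error is conservative.** With positive correlation, false positives fall below 5%; only negative correlation would inflate them. This is correct, but a test running at 0.8% is still not the 5% test the plan states.
- **The table uses normal data, which would go to the t test.** For skewed data (lognormal, log-SD 0.8) the null rates are essentially unchanged. When the change acts on the log scale, the power gap narrows to 30% against 52% at r = 0.5 and 28% against 74% at r = 0.7. The power loss is also not universal. In a further 4,000-run check with the same lognormal shape and a change of 0.5 raw-scale SD added to every value, power was 82% against 80% at r = 0.5 and 85% against 91% at r = 0.7. The distorted null distribution is therefore the firm part, and the power loss depends on how the change acts.
- **It is probably a drafting slip,** with the between-group test repeated one sentence early. That is plausible, but the Trial status section presents this version as definitive and nothing in the article corrects it.
- **A separate analysis plan might settle it.** That would excuse a test left unnamed. Here a test is named, and a later plan could only contradict it.

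**Conclusion.** The rule is wrong as written: Kruskal-Wallis H is not a valid test of change within the same participants. That conclusion follows from the test's independence assumption and rests on none of the assumed values.

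The size does rest on assumptions. With 22 per group and correlations from 0.3 to 0.7, the true false-positive rate is about 2.2% down to 0.1% instead of 5%. For normal data with a 0.5 SD change, power falls by 12 percentage points at r = 0.3, 27 at r = 0.5 and about 51 at r = 0.7. At zero correlation there is no meaningful difference, but that is implausible for repeated measurements on one person. Real changes would usually be missed more often.

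The damage is confined to within-group results for variables that fail the normality test. The paired t test branch and the between-group analysis are not affected.

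**What to change.** In the within-group sentence of the Statistical analysis section, replace Kruskal-Wallis H with the Wilcoxon signed-rank test for each follow-up against the pre-evaluation. If all four visits are to be compared together, name the Friedman test with paired post hoc tests instead. Keep Kruskal-Wallis H for comparisons between the three arms only.

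The cost is one phrase. Both tests are available in the software the article names, and the design, sample size and data collection stay as they are. The correction should be recorded before the data are analysed.

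### The between-group test named in the plan uses no information from other visits, so on observed data participants lost by week 12 leave that comparison; a mixed model on scores already collected is a better choice

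*Protocol article*

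**What the plan says.** Three parts of the protocol article bear on this.

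- **Statistical analysis.** "For the intergroup hypothesis contrast, one-factor analysis of variance (ANOVA) will be used in the case of parametric distributions"; otherwise Kruskal-Wallis is used. Post hoc comparisons are by Bonferroni or Mann-Whitney, and within-group changes by paired tests. No model joining the visits is named. The software is SPSS 24.
- **Sample size calculation.** The allowance and its result are given together: "a rate of follow-up losses of 15%, 10 subjects are required in each group". Enrolment is then raised to 66, with at least 20 per group, expressly to absorb losses.
- **Outcome measures, Overall Balance Index (OBI).** All four outcomes (OBI, VAS, PPT and NDI) are taken before treatment and at the "first evaluation (week 2), second evaluation (week 4, short-term), and third evaluation (week 12, medium term").

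The article does not state an analysis population, a way of handling missing scores, or whether the ANOVA is run at each visit or on change scores.

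**The concern.** A one-factor ANOVA has group as its only factor. With four measurement times it has to be applied to one visit, or one change score, at a time. That follows from the test named, although the article does not say it. Run on observed data, it leaves out anyone without a score at the visit tested. A participant lost between weeks 4 and 12 has three sets of scores, and none of the post-baseline ones contributes to the week-12 contrast.

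Extra enrolment restores the number of participants but does not undo selection. If those who leave differ from those who stay, and do so differently by arm, the medium-term difference partly reflects who remained. This is conceivable here because the arms differ in burden. The exercise arm trains daily for three weeks, building from two exercises to six. The sham arm receives a brief hand contact and an inactive laser pointer, and is promised one of the treatments after completing the study.

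The point concerns participants who leave of their own accord. It does not concern those excluded under the Interventions section for interference with treatment.

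**Working it through.** **Inputs from the Sample size calculation section.** Alpha 0.05, power 90%, SD 0.10, difference 0.098, loss 15%, three groups, 66 enrolled (22 per group if equal). In SD units the planned difference is 0.098 / 0.10 = 0.98.

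**1. The plan's own figure.** Noncentral-F power for a three-group one-way ANOVA, with group means evenly spaced 0.098 apart, reaches 90% at n = 8 per group. Then 8 / (1 - 0.15) = 9.4, rounded up to 10, which matches the stated 10 per group. Of the readings tried, only this one matches. With 0.098 between the extreme means, for example, n is 28, or 33 after loss.

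**2. Size of the loss.** 66 x 0.15 = 9.9, about 10 participants. 66 x 0.85 = 56.1 remain, or 18.7 per group. That exceeds the stated requirement of 10, so on the plan's own figure the issue is possible bias and not a power shortfall.

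**3. Simple bound on the bias.** Suppose 15% are lost per arm and, in one arm only, those lost differ from those kept by delta. The bias of the observed-data difference is 0.15 x delta:

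| delta (SD) | bias (SD) | share of 0.98 SD |
|---|---|---|
| 0.25 | 0.0375 | 4% |
| 0.5 | 0.075 | 8% |
| 1.0 | 0.15 | 15% |

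If delta is zero, or the same in every arm, the bias is zero.

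**4. Simulation.** The following are assumptions, not figures from the documents: two arms of 22, equal true means, the same correlation r between all visits, and loss before week 12 following a logistic model on the week-4 score (log-odds 1 or 2 per SD), 15% overall, 4000 trials per scenario. The Monte Carlo error of each bias is about 0.32 / sqrt(4000) = 0.005 SD.

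Bias of the observed-data week-12 difference, in SD:

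| Loss by arm | r | log-odds 1 | log-odds 2 |
|---|---|---|---|
| 10% / 20% | 0.5 | 0.042 | 0.064 |
| 10% / 20% | 0.7 | 0.048 | 0.090 |
| 5% / 25% | 0.5 | 0.082 | 0.114 |
| 5% / 25% | 0.7 | 0.118 | 0.162 |

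Repeat runs agree to about 0.01 SD. With 15% loss in both arms the bias is at most 0.01 SD.

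The largest value is 0.162 / 0.32 = 0.51 of a standard error and 0.162 / 0.98 = 17% of the planned difference.

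**5. The alternative in the same simulations.** An estimate that uses baseline and weeks 2 and 4 (equivalent to maximum likelihood when loss is monotone) has bias under 0.01 SD throughout. Its precision depends on how baseline enters:

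- Baseline as just another visit, with a free mean in each arm: standard error 0.31 to 0.33, little different from the observed-data test.
- Baseline as a covariate, or with one mean common to all arms: standard error 0.23 (r = 0.7) to 0.29 (r = 0.5), against about 0.32.

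The gain in precision therefore comes mainly from baseline adjustment, and the removal of bias from using the earlier visits.

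**The case against.** The strongest case on the other side is that the article lists tests and says nothing about missing scores. A reader might infer that these tests can use only attendees. They can also be run on imputed data, and imputation is a detail an article commonly leaves to a fuller document. That stands: the absence of a missing-data rule is no fault here. What remains is a choice the article does make, a test that carries nothing over from other visits.

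A reader might also take 15% as the expected absence at week 12. It is a sample-size allowance, and the article does not say when losses fall.

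Nor does any section show that loss will be selective or differ by arm. The deferred treatment promised to the sham arm, and the stated blinding of participants, could instead help to retain that arm.

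The simulation is kind to the mixed model: loss depends on the week-4 score, which that model uses, so missing-at-random holds by construction. If loss came before week 4, or depended on unobserved later pain, the advantage would shrink or vanish.

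The effect is also modest. With a standard error of 0.32, a bias of 0.09 SD raises a two-sided 5% pairwise test to about 6%, and 0.16 SD to about 8%, before any Bonferroni step. All of this limits the size of the point. None of it favours the one-factor test over a model that is available at little cost.

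**Conclusion.** The concern holds as a choice of method that should be improved, not as a demonstrated bias. The named between-group test ignores the other visits. If the allowed loss occurs by week 12 and the test is run on observed data, about 10 of 66 participants leave that comparison. The bias is then about 0.04 to 0.16 SD under the assumed unequal and selective losses, at most about half a standard error. It is negligible if loss is random or alike across arms.

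The stronger reading, that the week-12 result will be biased by selective loss, is not supported: the documents give neither the pattern of loss nor its timing. The count rests on 15% and 66. The bias range rests wholly on the assumed splits, correlations and dependence on the week-4 score. The change is worth making because it rests on a weaker missing-data assumption and, with baseline adjustment, is more precise.

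**What to change.** In the Statistical analysis section, make the between-group analysis of each outcome one linear mixed model:

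- all available scores from randomised participants;
- arm-by-visit means and an unstructured covariance across visits;
- baseline as a covariate, or with one mean common to all arms;
- a small-sample degrees-of-freedom correction, given about 22 per arm.

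Read the week-4 and week-12 contrasts from this model. Keep the per-visit ANOVA or Kruskal-Wallis as a sensitivity analysis, which also covers doubt about normality. The wording should say how participants excluded under the Interventions section are treated in the analysis, since the article leaves that open. The paired tests and the pain-stability correlations are outside this change and would still use whatever scores are observed.

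The cost is a change of wording and a little more analysis work. It needs no new data or visits, and mixed models can be fitted in the software already named. The downside is reliance on missing-at-random given the earlier visits, which the data cannot confirm.

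### The between-group test names no adjustment for the baseline value that the trial already measures, so it gives up precision that ANCOVA would recover at almost no cost

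*Protocol article*

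**What the plan says.** The Statistical analysis section of the protocol article fixes the comparison of the three arms: "For the intergroup hypothesis contrast, one-factor analysis of variance (ANOVA) will be used in the case of parametric distributions". Kruskal-Wallis replaces it when normality fails. Post hoc comparisons are Bonferroni contrasts or Mann-Whitney tests respectively. Group is the only factor, no covariate is named, and the section does not say whether the ANOVA is run on follow-up values or on changes from baseline. It also puts the power of the study at 90%.

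Baseline is available for every outcome. After describing the NDI, VAS, PPT and OBI, the article says: "These variables will be measured in the pre-evaluation, first evaluation (week 2), second evaluation (week 4, short-term), and third evaluation (week 12, medium term").

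The Sample size calculation section uses "a unilateral contrast", an alpha of 0.05, a beta of 0.10, "a typical deviation of 10% (0.10"), a difference of 0.098 and 15% losses. It arrives at 10 per group and then plans 66 patients in three groups.

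**The concern.** When the same measure is taken before and after randomisation, the baseline value usually explains part of the spread at follow-up. A test with group as its only factor leaves that spread in the error term. On change scores it removes some of it, but with a fixed slope of 1, which is generally not the best one. On follow-up scores, any chance difference between arms at baseline stays in the estimate as random error.

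The arms here have about 22 patients each. The eligibility criteria set no limits on baseline OBI, pain or disability, and the randomisation section describes no stratification. Precision is therefore worth having, most of all because the tests named for the analysis are more demanding than the one used to size the trial.

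**Working it through.** **Inputs.** From Sample size calculation: difference 0.098, SD 0.10 (standardised difference 0.98), alpha 0.05, power 0.90, one-sided, 15% losses, 66 patients. So 66/3 = 22 per arm and 22 × 0.85 = 18.7 evaluable per arm. From Statistical analysis: overall F test at 0.05, and Bonferroni over three pairs (two-sided 0.05/3). **Assumed:** the correlation r between baseline and follow-up, which the article does not give.

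**The plan's own figure.** For two groups, one-sided: n = 2 × (1.645 + 1.282)² / 0.98² = 17.8, so 18; 18/0.85 = 21.2, so 22 per arm and 66 in total. The 66 fits the stated inputs; the 10 per group does not, which is a separate matter. With 18.7 per arm, one-sided power is 91% by the normal approximation and about 90% by noncentral t.

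**Power of the named tests, unadjusted** (0.10 as the follow-up SD, error df 3 × 18.7 − 3 = 53.1):

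- Overall F, means 0 / 0.049 / 0.098: noncentrality 18.7 × (0.049² + 0.049²)/0.10² = 8.98; power 74.4%.
- Overall F, means 0 / 0 / 0.098: noncentrality 18.7 × (2/3) × 0.098²/0.10² = 11.97; power 86.3%.
- One Bonferroni pair, pooled error: noncentrality 0.98 × √(18.7/2) = 3.00; power 69.9%. (The normal approximation gives 72.7%.)

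**With ANCOVA.** Residual variance is multiplied by 1 − r² and one error df is lost (52.1):

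| r (assumed) | 1 − r² | Overall F, third arm midway | Bonferroni pair |
|---|---|---|---|
| 0.3 | 0.91 | 79% | 75% |
| 0.4 | 0.84 | 82% | 78% |
| 0.5 | 0.75 | 86% | 83% |
| 0.6 | 0.64 | 91% | 89% |
| 0.7 | 0.51 | 96% | 95% |

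Reaching 90% needs r of about 0.57 for the midway F test and about 0.61 for the Bonferroni pair. With two arms equal, the F test needs only about 0.33.

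**If the ANOVA is run on change scores.** With equal SDs at both visits, the change has variance 2(1 − r) times the follow-up variance. That exceeds 1 for r below 0.5, equals 1 at 0.5, and is never below 1 − r², because 2(1 − r) − (1 − r²) = (1 − r)². Change scores therefore do not remove the point.

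**If 0.10 is the SD of change.** The unadjusted change-score analysis then has the 74% and 70% above. ANCOVA multiplies that variance by (1 − r²)/[2(1 − r)] = (1 + r)/2. At r = 0.5 the factor is 0.75 and power is 86% (F) and 83% (pair). At r = 0.7 the factor is 0.85 and power is 81% and 78%. Under this reading the gain shrinks as r rises.

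**The case against.** A reader might infer that the trial lacks power and that baseline adjustment would restore it. The article does not support that as stated. On its own one-sided, two-group terms, 66 patients give about 90%. The gap appears only when those terms are set against the F test and Bonferroni contrasts of the analysis section, and that mismatch needs reconciling in its own right. The 74% also depends on the third arm lying midway. The stated hypothesis is that both active arms beat sham; if the two do so equally, F-test power is already 86%. Whether adjustment reaches 90% rests on an undocumented correlation. OBI is the score of a single 20-second test followed over up to 12 weeks, so the article gives no ground for presuming r of 0.5 or more. All of this stands.

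A reader might also infer that the planned analysis ignores baseline altogether, or that it is biased. The first is not established, since the ANOVA may be on change scores. The second is wrong: under randomisation the unadjusted comparison is unbiased, and chance imbalance is sampling variation, the same precision point seen from another side.

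Finally, an article condenses a longer protocol, and covariates are often left to an analysis plan. That would answer a silent article. This one names a specific one-factor test and describes itself under Trial status as the definitive version, so the choice of test is open to comment.

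None of this touches the core: adjustment gains precision at any non-trivial correlation.

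**Conclusion.** The point holds as one of efficiency. The named between-group tests are valid, but they include no baseline adjustment although every outcome has a baseline value, and they are generally less precise than ANCOVA. With 0.10 as the follow-up SD, the variance saved is r²: 9% at r = 0.3, 25% at 0.5, 49% at 0.7. At r = 0.5 that is worth 22/0.75 = 29 per arm instead of 22. The power gained is about 4 to 5 points at r = 0.3 and 12 to 14 at r = 0.5, from 74% (midway F test) and 70% (Bonferroni pair). It closes the gap to 90% only if r is near 0.6 or above, or at lower r if two arms share a mean. If 0.10 is the SD of change, the same sums apply with the factor (1 + r)/2. All figures assume 15% loss, a common SD across arms and a linear baseline relation; the values of r are illustrative.

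**What to change.** Before any between-group results are seen, replace the one-factor ANOVA with one of the following:

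- ANCOVA at each follow-up, with the outcome modelled on group plus the pre-evaluation value of the same outcome; or
- one mixed model over weeks 2, 4 and 12 with baseline, group, visit and group-by-visit, which also uses the data of participants lost before week 12.

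Report adjusted mean differences with 95% confidence intervals and Bonferroni-adjusted pairwise contrasts, and treat the within-group tests as descriptive. Judge normality on the model residuals. If they are clearly non-normal, keep the adjustment, for example with a transformed outcome or a rank-based ANCOVA, and do not revert to unadjusted Kruskal-Wallis and Mann-Whitney tests. State whether the SD of 0.10 refers to follow-up values or to change.

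The cost is one degree of freedom for the covariate and slightly more analysis work. No extra patients or measurements are needed, and the named software can fit these models.
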